## Abstract

**Background:**

Prognostic models in reproductive medicine can help to identify subfertile couples who would benefit from fertility treatment. Expectant management in couples with a good chance of natural conception, *i.e.*, tailored expectant management (TEM), prevents unnecessary treatment and is therefore recommended in international fertility guidelines. However, current implementation is not optimal, leaving room for improvement. Based on barriers and facilitators for TEM that were recently identified among professionals and subfertile couples, we have developed a multifaceted implementation strategy. The goal of this study is to assess the effects of this implementation strategy on the guideline adherence on TEM.

**Methods/design:**

In a cluster randomized trial, 25 clinics and their allied practitioners units will be randomized between the multifaceted implementation strategy and care as usual. Randomization will be stratified for *in vitro* fertilization (IVF) facilities (full licensed, intermediate/no IVF facilities). The effect of the implementation strategy, *i.e.*, the percentage guideline adherence on TEM, will be evaluated by pre- and post-randomization data collection. Furthermore, there will be a process and cost evaluation of the strategy. The implementation strategy will focus on subfertile couples and their care providers *i.e.*, general practitioners (GPs), fertility doctors, and gynecologists. The implementation strategy addresses three levels: patient level: education materials in the form of a patient information leaflet and a website; professional level: audit and feedback, educational outreach visit, communication training, and access to a digital version of the prognostic model of Hunault on a website; organizational level: providing a protocol based on the guideline. The primary outcome will be the percentage guideline adherence on TEM. Additional outcome measures will be treatment-, patient-, and process-related outcome measures.

**Discussion:**

This study will provide evidence about the effectiveness and costs of a multifaceted implementation strategy to improve guideline adherence on TEM.

**Trial registration:**

http://www.trialregister.nlNTR3405. This study is sponsored by ZonMW.

## Background

Subfertility is defined as the absence of conception after one year of unprotected intercourse [1]. It affects approximately 9% of all couples of reproductive age [2,3]. In approximately 50% of the couples, no major cause is found after the basic fertility work-up [4]. In those couples, the chance of natural conception can be calculated via validated prognostic models [5,6]. If the chance of natural conception within one year is good, meaning a probability of 30% or more, expectant management for 6 to 12 months is equally effective as treatment [7]. Because this expectant management is restricted to couples with a good prognosis, we have called it tailored expectant management (TEM).

European Society of Reproductive Medicine (ESHRE) and National Institute of Health and Clinical Excellence (NICE) guidelines on the management of infertility both emphasize that couples should not be exposed to unnecessary risks or ineffective treatments and encourage that each subfertile couple should receive information about the estimate of their chance of natural conception [8,9]. In the Netherlands, the national network guideline on infertility for gynecologists and general practitioners (GPs) explicitly recommends the use of prognostic models and subsequent TEM for couples with unexplained or mild infertility [10]. However, at this moment, implementation of TEM is poor. A recent Dutch multicenter cohort study showed overtreatment in 36% of the couples, *i.e.*, 36% of the couples with a good prognosis eligible for TEM (>30% chance of natural conception in one year) already started medically assisted reproduction (MAR) [11].

This overtreatment in subfertile couples is worrisome for several reasons. First, fertility treatment still leads to a considerable number of multiple pregnancies, which are associated with a higher morbidity and mortality in both mothers and neonates [12]. Second, fertility treatment carries a significant physical and psychological burden and accompanying productivity loss [13-16]. Third, fertility treatment and its complications are expensive and put considerable financial strain on societies where MAR is reimbursed or on the subfertile couples in societies where MAR is not or only partially reimbursed [17].

The first step to improve guideline adherence on TEM and reduce overtreatment is to gain insight into barriers and facilitators for implementation of TEM and MAR reduction. Subsequently a tailored implementation strategy can be developed targeting obstacles to change, if necessary at different levels [18,19]. In a previous qualitative and quantitative study among patients and professionals, the main barriers among subfertile couples were lack of confidence in natural conception, perception that expectant management is a waste of time, inappropriate expectations prior to the first secondary care consultation, and an overestimation of the success rates of treatment. Both couples and professionals regarded the lack of patient information materials as an important barrier. Among the professionals, limited knowledge about prognostic models and limited communication skills to convince the couple, both leading to a decision in favor of treatment, were recognized as main barriers. Facilitators experienced by the professionals were better management of patients’ expectations, local consensus, and the presence of a local protocol and local fertility meetings [11,20].

A multifaceted implementation strategy to improve guideline adherence on TEM has now been developed based on these data. The aim of this study is to evaluate effectiveness and costs of this implementation strategy in a cluster randomized trial.

## Methods

### Setting

In the Netherlands, subfertile couples are usually referred by the GP to secondary care. GPs usually perform only limited basic fertility workup or no workup at all and they do not prescribe fertility drugs. Secondary and tertiary care is provided by three different types of fertility clinics based on the kind of treatment they offer. Initial fertility assessment, ovulation induction (OI), and intra-uterine insemination (IUI) are carried out in all Dutch clinics. In vitro fertilization (IVF) and intracytoplasmic sperm injection (ICSI) treatments are only carried out in intermediate and licensed fertility clinics. Every Dutch citizen has a basic insurance coverage, which fully reimburses all treatment cycles of OI and IUI, with or without controlled ovarian hyperstimulation, as well as a maximum of three IVF or ICSI cycles.

### Study design

We propose a cluster randomized trial in 25 clinics and their allied GP units with an effect, process, and economic evaluation alongside the trial.

### Randomization

The 25 participating clinics and their allied practitioners units will be randomized between the multifaceted implementation strategy and care as usual. Randomization will be stratified for IVF facilities (full licensed, intermediate/no IVF facilities) and will take place after all clinics have approval to participate. Randomization will be done by an independent physician and will be computer-generated. Results of the randomization will be personally communicated to all participating clinics.

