### Sample size

The expected adherence to TEM in the control arm is estimated based on previous studies at 60% [11]. To increase this to 80% with an intra-class correlation (ICC) of 0.1, alpha at 5%, comparing two strategies, we estimate that with 25 clusters we would need a total sample size of 450 patients. This means we need to include 15 to 20 patients per clinic in the baseline as well as in the after measurement.

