### Data analysis

To analyze the effectiveness of the implementation strategy, descriptive statistics and multilevel analysis will be used. The statistical analysis will be performed using SPSS version 16.0 for Windows.

The main outcome, the difference in baseline and after-measurement scores in guideline adherence on TEM, between the intervention and control group will be analyzed with the chi-square test.

Descriptive analysis will be used to assess the difference in treatment-related, treatment outcome-related, and patient-related measurements between the intervention and control group. Furthermore, time to pregnancy and time to start fertility treatment will be analyzed using Kaplan Meier analysis with log-rank test. Univariate and subsequent multivariate logistic and Cox regression analyses will be used to analyze the relative contribution of the implementation strategy versus other predictive factors for guideline adherence on TEM.

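### The chi-square named for the main outcome accounts for neither the clinic nor the IVF-facility stratum used in randomisation; the primary analysis should be clustered, with the stratum as a term

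*Protocol article*

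**What the plan says.** All statements are in the Protocol article.

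- **Randomization:** the unit is the clinic. "The 25 participating clinics and their allied practitioners units will be randomized between the multifaceted implementation strategy and care as usual". The same section adds that "Randomization will be stratified for IVF facilities (full licensed, intermediate/no IVF facilities"). It gives no reason for the stratification and no number of clinics per stratum.
- **Data analysis:** the section opens by saying that for effectiveness "descriptive statistics and multilevel analysis will be used". It then names the test for the main outcome: the change in adherence "between the intervention and control group will be analyzed with the chi-square test". No clinic or stratum term is attached to that test. Later regression models are meant to "analyze the relative contribution of the implementation strategy versus other predictive factors for guideline adherence on TEM"; the IVF stratum is not named there either.
- **Sample size:** "The expected adherence to TEM in the control arm is estimated based on previous studies at 60" percent. The calculation continues "To increase this to 80% with an intra-class correlation (ICC) of 0.1, alpha at 5" percent, and concludes that "with 25 clusters we would need a total sample size of 450 patients". Clustering is therefore recognised when the trial is sized.

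**The concern.** The design has two features that the analysis should reflect: clinics, not couples, are randomised, and they are randomised within IVF-facility strata. The test named for the main outcome uses neither.

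The two gaps act in different directions and differ in size. Ignoring the clinic treats correlated couples as independent, so the standard error is understated and a strategy with no effect is declared effective too often. Ignoring the stratum, in an analysis that does respect clinics, leaves any difference between clinic types in the error term, so the test is somewhat conservative and loses power. With 25 clinics the between-clinic part dominates the variance, so both matter for the main conclusion. The first gap is much the larger.

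**Working it through.** **Inputs from Sample size:** adherence 60% v 80%, ICC 0.1, alpha 5%, 25 clinics, 450 couples, hence 450/25 = 18 per clinic. Power and sidedness are not stated; 80% and two-sided are assumed. As in that section, the calculations compare the arms at a single measurement.

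**1. The protocol's own figure.** The two-proportion formula with pooled variance under the null gives (1.96 × √(2 × 0.7 × 0.3) + 0.842 × √(0.24 + 0.16))² / 0.2² ≈ 81.2, so 82 per arm. The design effect is 1 + (18 − 1) × 0.1 = 2.7. Then 82 × 2.7 = 221.4, so 222 per arm and 444 in total, against the stated 450. The figure reproduces, and it depends on the clustering.

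**2. Standard error of the difference, with and without clinics.**
- Couples as independent: √((0.24 + 0.16)/225) = √(0.40/225) = 0.042.
- Clinics respected: the per-clinic variance factor is 0.10 + 0.90/18 = 0.15, with 12.5 clinics per arm on average. √(0.40 × 0.15/12.5) = 0.069.
- Ratio 0.069/0.042 = √2.7 ≈ 1.64. The chi-square's error bars are too narrow by that factor.

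**3. Type I error of the couple-level chi-square by formula:** 2 × (1 − Φ(1.96/√DE)), where DE is the design effect.
- 15 per clinic: DE 2.4, 21%.
- 18 per clinic: DE 2.7, 23%.
- 20 per clinic: DE 2.9, 25%.

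At 450 couples, power is 81% with the design effect. A calculation that treats couples as independent would claim 99.7%.

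**4. What the stratum adds.** This was simulated with 25 clinics of 18 couples, stratified allocation and 6,000 runs per scenario. Total between-clinic variance, including the stratum, is 0.1 × 0.24 = 0.024. The number of clinics in the smaller stratum (5 or 10) and the adherence gap between strata are assumptions. The share of between-clinic variance due to the stratum is f(1 − f) × gap²/0.024, with f = 5/25 or 10/25. MH is the Mantel-Haenszel test by stratum, still on couples. The cluster-level tests use clinic proportions.

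| Clinics in smaller stratum | Gap (points) | Share | Type I: chi-square | Type I: MH | Type I: cluster-level, without / with stratum | Power: cluster-level, without / with stratum |
|---|---|---|---|---|---|---|
| 5 | 0 | 0% | 24% | 24% | 5.3% / 5.5% | 73% / 73% |
| 5 | 10 | 7% | 23% | 23% | 4.6% / 5.3% | 74% / 75% |
| 5 | 15 | 15% | 23% | 22% | 4.3% / 5.4% | 74% / 77% |
| 5 | 20 | 27% | 18% | 18% | 3.1% / 4.5% | 74% / 80% |
| 10 | 0 | 0% | 24% | 24% | 4.9% / 4.9% | 72% / 72% |
| 10 | 10 | 10% | 22% | 23% | 3.7% / 4.4% | 74% / 76% |
| 10 | 15 | 22.5% | 20% | 21% | 3.6% / 4.8% | 75% / 80% |
| 10 | 20 | 40% | 15% | 16% | 2.1% / 4.5% | 75% / 85% |

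Adding the stratum to the couple-level test changes almost nothing. Adding it to the cluster-level test gains from nothing to 10 points of power and brings a conservative test back to about 5%.

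The cluster-level powers lie below the 81% of step 3 for two reasons. They use small-sample t-tests, and between-clinic variance is held at 0.024 in both arms, which is an ICC of 0.024/0.16 = 0.15 in the arm at 80%.

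**5. Normal-approximation cross-check of a favourable case.** If clinic type explained 20% or 30% of between-clinic variance, the factor 0.15 would fall to 0.08 + 0.05 = 0.13 or 0.07 + 0.05 = 0.12. Power would rise from 82% to 87% or 90%. That share requires a gap between clinic types of √(0.2 × 0.024/0.24) = 14 to √(0.3 × 0.024/0.24) = 17 points with 10 clinics in the smaller stratum. With 5 clinics it is 17 to 21 points, using 0.16 in place of 0.24. Such gaps are close to the 20-point treatment effect itself.

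**The case against.** The strongest reply is that a journal article condenses the plan. Covariate lists usually sit in the analysis plan, the article does name multilevel analysis and regression with other predictive factors, and nothing excludes the IVF stratum from those models. This stands for the secondary regression and time-to-event models: their silence on the stratum is no fault. It does not cover the main outcome, because there the article names a specific test, and a chi-square as written has no place for either clinic or stratum. An analysis plan that included them would have to depart from it.

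A second reply is that the value of the stratum is unproven. The protocol gives no reason for choosing it, no stratum sizes and no adherence by clinic type, and its Setting section says only which treatments each clinic type offers. This stands, and it is why the gain is given as a range that starts at nil.

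A reader might also infer that the unstratified chi-square wastes precision, so that its error bars are too wide, or that matching the test to the stratification would restore the error rate. The documents support neither. The randomised unit is the clinic and the protocol's ICC is 0.1, so the couple-level test has error bars that are too narrow, and stratifying it leaves the type I error at 16-24%.

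**Conclusion.** The mismatch is in the text. Clinics are randomised within IVF-facility strata, and the test fixed for the main outcome uses neither clinic nor stratum. It also conflicts with the ICC-based sample size and with the multilevel analysis announced in the same section.

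- **Missing clinic term (the main fault):** the standard error is about 0.042 where about 0.069 is needed, and type I error is roughly 15-25% against 5%. This assumes that the chi-square is applied to couples, that the ICC is 0.1 and that there are 15 to 20 couples per clinic.
- **Missing stratum term (a smaller, separate fault):** it costs precision only once clustering is respected. Including the stratum then gains about 0 to 10 power points under assumed stratum sizes of 5 or 10 clinics and gaps of 0 to 20 points. The gain could be nil.

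It would go too far to conclude that the plan overlooks clustering altogether, since the sample size and the multilevel sentence both recognise it. The mismatch itself is certain; the size of the gain from the stratum is not.

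**What to change.** In Data analysis, replace the chi-square as the test of the main outcome with a primary analysis that respects clinics: either the multilevel model already mentioned there or a cluster-level analysis. Include the IVF-facility stratum used in randomisation as a fixed effect in the model, or stratify the cluster-level analysis by it. A chi-square on couples could remain as description only. Adding the stratum to the chi-square is not a substitute.

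The stratum is known for every clinic, so no data need to be added. The cost is one clinic-level degree of freedom, if the stratum has two levels; the punctuation in Randomization leaves room for three, which would cost two, so the levels should be stated. With no adherence gap between strata, the simulation shows essentially no loss of power. According to Trial status the baseline measurement is still under way, so the change can be made before any after-measurement data exist.

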### Effectiveness

For the effectiveness, a baseline measurement will be performed in all participating clinics, including guideline adherence on TEM, and a range of organizational, professional, and patient characteristics (see outcome measures). Following baseline measurement, the multifaceted implementation strategy will be applied in the intervention clinics. After ten to twelve months of intervention exposure, the after measurement will be performed again in all 25 participating clinics.

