### Professional level (*e.g.*, gynecologists (in training), fertility doctors, and GPs)

The strategy regarding the professionals contains audit and feedback, an education outreach visit, supportive consultation tools, and a video-based communication training.

The audit and feedback of the current care will consist of a feedback report based on the results of the baseline measurement. This feedback will report clinic’s guideline adherence on TEM in a twelve-month period prior to the randomization compared with the other participating clinics. It will give insight in how they are adhering to the guideline concerning the policy for couples with unexplained or mild infertility, *e.g.*, use of prognostic models and subsequent TEM in case the prognosis is good. Furthermore, the report will provide feedback on patient-related measures like general experiences with fertility care, specific experiences with the prognostic model and TEM, quality of life, and trust in their physician [ref].

In addition to this audit and feedback, an educational outreach visit will take place with fertility doctors and gynecologists (in training), in which background information about how and when to use the prognostic model of Hunault, and subsequent TEM will be given and in which the results of the baseline measurement and local barriers will be discussed. The result of this visit will be an individualized action plan per clinic.

The supportive consultation tools are developed containing a digital version of the prognostic model of Hunault on a website and we will provide professionals with a summary of the guideline on TEM in the form of a pocket card.

Finally, a video-based training strategy will be provided to improve the communication techniques to counsel the patients on their chance of spontaneous conception versus conception after treatment, the (dis)advantages of expectant management versus fertility treatment, and on the reason for TEM (*i.e.*, making clear it is not a waste of time). Consistent with functional models of medical communication described in the field [24], the LEAPS Framework, a pneumonic for Listen, Educate, Assess, Partner and Support will be used to develop the intervention [25].

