### Trial status

We are currently performing the baseline measurement in all participating clinics.

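### With 25 clinics balanced only on IVF facilities, the main comparison should adjust for each clinic's baseline adherence instead of testing an unadjusted change by chi-square

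*Protocol article*

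**What the plan says.** All references are to the protocol article.

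- **Randomization.** "The 25 participating clinics and their allied practitioners units will be randomized between the multifaceted implementation strategy and care as usual". Allocation is computer-generated by an independent physician. The only restriction named is the two-level IVF factor, and the timing is tied to clinic approval: "Randomization will be stratified for IVF facilities (full licensed, intermediate/no IVF facilities) and will take place after all clinics have approval to participate". The whole set of clusters is therefore known before any is allocated. No allocation ratio is given.
- **Effectiveness** (under Methods). "a baseline measurement will be performed in all participating clinics, including guideline adherence on TEM". The strategy is applied in the intervention clinics after that.
- **Abstract, Methods/design.** The effect "will be evaluated by pre- and post-randomization data collection".
- **Professional level.** The feedback report covers "guideline adherence on TEM in a twelve-month period prior to the randomization".
- **Trial status.** "We are currently performing the baseline measurement in all participating clinics". The Randomization section still speaks of allocation in the future tense.
- **Data analysis.** The main outcome is the baseline-to-after difference in adherence, compared between arms by chi-square. Multilevel analysis is mentioned in general terms, and multivariable regression is planned for predictors of adherence. Neither is made the main test, and clinic baseline adherence is not named as a covariate.

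**The concern.** With about a dozen clinics per arm, one binary stratification factor does little to equalise clinics that differ in how often they already follow the guideline. A sizeable baseline gap in the primary outcome is therefore a realistic result of a single draw.

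The planned comparison does not handle such a gap well. Subtracting baseline treats each point of observed gap as if it would persist in full. Part of it is sampling noise from 18 couples per clinic, and part is drift in clinic practice between waves, so some of the gap disappears by itself. The change contrast then credits or debits that disappearance to the strategy. The baseline data that would correct for this are already being collected, so leaving them out of the main model as a covariate gives up precision and weakens the reading of whichever allocation is drawn.

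**Working it through.** **Inputs from the Sample size section:** control adherence 60%, target 80%, ICC 0.1, alpha 5%, 25 clusters, 450 couples in total. 450/25 = 18 couples per clinic, within the stated 15 to 20.

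**Assumptions of this check:** 12 v 13 clinics; two-sided alpha; 80% power (none is stated); equal cluster sizes; the same variance in both waves; correlation ρ between a clinic's true adherence rates in the two waves.

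**1. The protocol's own figure.** 60% v 80% at 80% power needs 82 per arm without clustering. The design effect is 1 + (18 − 1) × 0.1 = 2.7. Then 2 × 82 × 2.7 = 443, within 2% of 450. The inputs are usable as read.

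**2. Baseline gap between arms.**
- Variance of a clinic's observed rate: 0.6 × 0.4 × [0.1 + 0.9/18] = 0.24 × 0.15 = 0.036 (SD 0.190).
- SE of the arm difference: √[0.036 × (1/12 + 1/13)] = √(0.036 × 0.1603) = 0.076.
- P(|gap| ≥ 10 points) = 2 × [1 − Φ(0.10/0.076)] = 18.8%. A beta-binomial simulation with 200,000 runs gives 19.0%.
- P(|gap| ≥ 15 points) = 4.8%.

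**3. How far that figure moves.**

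| Variation | P(gap ≥ 10 points) |
|---|---|
| 15 / 20 couples per clinic | 20% / 18% |
| ICC 0.05 / 0.15 | 11% / 25% |
| IVF strata explain 10% / 25% / 50% of between-clinic variance | 17% / 15% / 11% |
| Underlying clinic rates only (variance 0.024, SE 0.062) | 11% |

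The 18.8% gives no credit to the IVF strata, so at ICC 0.1 and 18 couples per clinic it is an upper figure.

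**4. Effect of a gap on the change contrast.** The reliability of an observed clinic rate is 0.024/0.036 = 0.667. The correlation of observed rates between waves is r = 0.667ρ. Given an observed baseline gap g, the after-measurement gap expected without any effect is r × g, so the change contrast shifts by (1 − r) × g in size. For g = 10 points:

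| ρ (assumed) | r | Shift, points |
|---|---|---|
| 1.0 | 0.667 | 3.3 |
| 0.8 | 0.533 | 4.7 |
| 0.5 | 0.333 | 6.7 |

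Even with perfectly stable clinics the shift is not zero, because sampling noise remains.

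**5. Unadjusted change against baseline-adjusted comparison.**
- SD of the change contrast: √[2 × 0.036 × (1 − r) × 0.1603], which is 0.073 at ρ = 0.8 and 0.088 at ρ = 0.5.
- SD of the adjusted contrast with the slope known: √[0.036 × (1 − r²) × 0.1603], which is 0.064 and 0.072. Simulation, which also estimates the slope, gives about 0.065 and 0.073.
- For comparison, an after-only contrast has SD 0.076. At ρ = 0.5 the change contrast is therefore worse than ignoring baseline altogether.

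**6. What balancing the allocation adds.**
- Crossing the IVF strata with an above/below-median split on observed baseline adherence lowers the probability of a 10-point observed gap from 19% to about 3% to 8%. The range reflects assumed sizes of 6 to 13 clinics for one IVF stratum.
- Drawing from the best-balanced 10% of stratified allocations (6/19 strata assumed) removed all observed gaps above 5 points.
- Once the analysis is adjusted, the SD barely moves: 0.065 v 0.065 at ρ = 0.8, and 0.073 to 0.071 at ρ = 0.5.

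**The case against.** The strongest reply is that stratified, computer-generated allocation by an independent person is a valid design, that no passage contradicts it, and that chance imbalance is already part of the standard error. This stands. A reader might infer that a 10-point gap biases the trial by nearly 5 points. The documents do not support that: over randomisations the change contrast is unbiased, and the 3 to 7 points are a conditional shift given a gap that is absent at least about 81% of the time.

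A reader might also infer that balancing baseline adherence at allocation would settle the matter under any analysis. It would not. It balances observed rates with a reliability of 0.667, so differences in true adherence remain, and nearly all of the gain in precision comes from adjusting the analysis.

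Third, it is tempting to read the protocol as saying that every clinic's baseline rate will be known when allocation takes place. The Abstract, Effectiveness, Professional level and Trial status sections fit that reading, but none states it. Randomization waits for approval, not for completed baseline data, and the twelve-month period before randomisation dates the care audited, not the abstraction of records.

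Finally, the plan does measure baseline adherence, subtract it in the main contrast, and mention multilevel and multivariable models. That is partial handling. The named main test is still chi-square on the change, with no clinic-level baseline adjustment.

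**Conclusion.** The point holds as one about precision and credibility, not bias, and its weight falls on the analysis more than on the allocation. At the protocol's inputs, an observed baseline gap of 10 points or more, half the target effect, has a probability of at most about 19%. With credit for the IVF strata it is 17% to 11%, and for underlying rates about 11%. Given such a gap, the planned change contrast shifts by about 3 to 7 points. Adjustment for baseline reduces the SD of the contrast from about 0.073 to 0.065 at a between-wave correlation of 0.8, and from 0.088 to 0.073 at 0.5.

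These figures rest on a 12 v 13 split and an ICC of 0.1. The shift and the SDs also rest on a between-wave correlation that the protocol does not give. Its value changes the size but not the direction: across the range shown, the adjusted comparison is the more precise one.

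**What to change.** **Main change (Data analysis).** Make the primary analysis a comparison of after-measurement adherence between arms, at cluster level or by a multilevel model, with each clinic's baseline adherence and the IVF stratum as covariates. It replaces the unadjusted change tested by chi-square. The data are already being collected, so the cost is a rewritten paragraph, fixed before outcome data are seen.

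**Optional addition (Randomization).** First state whether all 25 baseline rates will be available before allocation. If they will, balance on them too, either with an above/below-median stratum within the IVF strata or by drawing one allocation at random from those that are well balanced. With the second method, check that no pair of clinics is always together or always apart, and report the restriction and reflect it in the analysis. The script is short. The real cost is time: each rate depends on retrospective selection, couples' permission and record abstraction, so allocation everywhere would wait for the slowest clinic. The extra precision is small once the analysis is adjusted; the benefit is mainly credibility with few clusters, and it cannot be obtained after allocation.
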